### 2.6 Randomization

Randomization will be applied using an automated balancing algorithm. The algorithm will aim to partition participants into groups based on the initial onboarding assessment to make the resulting groups as balanced as possible concerning the characteristics outlined in the study design section, i.e., (1) primary addiction type; (2) participation in addiction-related therapy; (3) gender; (4) age; (5) addiction severity; (6) abstinence duration. Following randomization, participants in groups 1–12 will receive access to the intervention modules following a 5-day delay. In conditions 1:10, participants get access to the short-term intervention module and one type of long-term intervention. In condition 11, participants get access to the short-term intervention module and all long-term interventions. In condition 12, participants get access only to the short-term intervention module.

Participants in the waitlist control group will be able to access all intervention materials 5 weeks following study enrollment (see Figure 1).

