### 2.8 Measures

Sociodemographic data include gender, age, and place of residence. Substance use-related questions include frequency of use, lifetime use, treatment seeking, and abstinence period (see Supplementary Tables 1, 2). The study includes EMA (three times a day) assessing several variables: craving, lapses, mood, arousal, pressure, anxiety, procrastination, loneliness, tiredness, anger, hunger, and uncertainty (see Supplementary Table 3).

Moreover, the questionnaire assessment will occur three times during the study period (see Table 2).

**TABLE 2 T2:** Timeline of the questionnaire assessment.

Assessment instrument	Baseline (week 1)	Follow-up (week 5)	Follow-up (month 6)
Socio-demographic questions	*x*		
Substances use-related measures			
Psychological dependence (SDS)	*x*	*x*	*x*
Alcohol (AUDIT)	*x*	*x*	*x*
Stimulants (DUDIT)	*x*	*x*	*x*
Psychopathological symptoms measures			
Depression and anxiety (HADS)	*x*	*x*	*x*
Psychological functioning measures			
Sensation seeking (BSSS)	*x*	*x*	*x*
Emotion regulation (DERS)	*x*	*x*	*x*
Impulsivity (UPPS-P)	*x*	*x*	*x*
Coping with stress (Mini-COPE)	*x*	*x*	*x*
Life satisfaction (SWLS)	*x*	*x*	*x*

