### 2.9 Data analysis

We will use factorial design mixed-effects models to compare questionnaire battery scores between experimental groups and the control across measurements. In addition, we will perform an interrupted time series analysis to compare the longitudinal effects of the introduction of different types of interventions on longitudinal EMA outcomes.

We will include participants who complete at least 21 EMA assessments spread across the intervention testing period of 5 weeks. Furthermore, for the 6-month follow-up intervention effects retention analysis, we will include participants who complete at least three EMA assessments within the follow-up period. Moreover, in each intervention group, we will retain participants who log onto the app and use the long-term and short-term self-guided intervention modules at least four times and once, respectively, defined as minimal therapeutic exposure. Finally, for the secondary outcome analysis, we will include participants who complete the baseline and at least one follow-up assessment.

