## 3 Discussion

This study protocol describes a randomized controlled trial designed to determine the effectiveness of self-guided psychological intervention modules delivered *via* a smartphone app (*Nałogometr*). We aim to examine whether and which interventions can effectively reduce craving and lapse risk in problematic alcohol or stimulant use. The embedded trial and analysis will evaluate the effectiveness of intervention modules for alcohol or/and stimulants use. In exploratory analyses, we investigate whether user engagement moderates or changes in psychological functioning measures (e.g., sensation seeking, impulsivity, stress coping, emotion regulation) mediate the effectiveness of the interventions. We hope to determine if these interventions delivered through mobile devices can be effective and contribute to future prevention or therapy addiction programs. The wide availability and accessibility of developed interventions are a substantial advantage. Mobile app interventions may reduce treatment barriers by staying anonymous and avoiding stigma and may be especially useful in places where professional help is unavailable (49–52). We plan a 6 months follow-up to conduct a longer-term evaluation and check the sustainability of the potential change in the user’s behavior–it is an essential factor for relapse prevention through the management of craving. Such a complex study of 13 conditions will allow us to understand better which long-term interventions are most effective. We include multiple intervention types to better assess their effectiveness across diverse individuals. One limitation of the present study could be that the participant dropout will be higher than expected based on previous research (53, 54). Due to the lack of personal contact with researchers and no additional incentives, e.g., prizes or monetary remuneration, the commitment to participate throughout the study may be lower, and motivation may decrease over time.

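### Secondary-outcome models exclude randomised participants with a baseline but no follow-up questionnaire; the group-by-time contrast is biased if baseline means are free by arm and severity-related dropout differs between arms

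*Protocol article*

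**What the plan says.** The protocol article plans three questionnaire waves (2.8 Measures: "the questionnaire assessment will occur three times during the study period"). Table 2 places them at baseline (week 1), week 5 and month 6. For the scores, section 2.9 Data analysis plans: "We will use factorial design mixed-effects models to compare questionnaire battery scores between experimental groups and the control across measurements". The same section then fixes who enters: "for the secondary outcome analysis, we will include participants who complete the baseline and at least one follow-up assessment". A person with one of the two follow-ups stays in; a person with neither is removed, although the baseline score is on file.

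Two other places bear on this. Section 2.6 Randomization balances the groups, including on addiction severity, before allocation: "The algorithm will aim to partition participants into groups based on the initial onboarding assessment". It also gives the arms different access: groups 1 to 12 get modules after 5 days, whereas "Participants in the waitlist control group will be able to access all intervention materials 5 weeks following study enrollment". The Discussion names as a limitation that "the participant dropout will be higher than expected based on previous research" and, with no researcher contact or incentives, that "the commitment to participate throughout the study may be lower, and motivation may decrease over time".

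Section 2.9 also carries a module-use rule ("in each intervention group, we will retain participants who log onto the app and use the long-term and short-term self-guided intervention modules", with minimum counts) and does not say whether it covers the questionnaire analysis.

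**The concern.** The exclusion is a positive rule in the article, not a detail left to an analysis plan, and the article states no all-randomised analysis beside it.

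The sentence on the mixed models suggests that baseline is one of the modelled time points, so that the treatment effect is a group-by-time contrast. If each arm has its own baseline mean in that model, the contrast in the retained set is the difference in mean change among people who returned at least one later questionnaire. Randomisation balanced the arms on severity at entry; selection on later completion can undo that balance. Where the retained arms differ at baseline, regression to the mean turns the gap into an apparent treatment difference. In the free-means model, the baseline scores of those lost are what allow the likelihood to correct for dropout related to baseline severity, and the rule discards them.

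At stake is whether the results for AUDIT, DUDIT, SDS, HADS and SWLS describe the effect in the people allocated or in those who came back.

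**Working it through.** **Inputs from the article.** The inclusion rule, the model and the three waves are as given above. No dropout rate, retention by arm, correlation or numerical effect size is stated. Section 2.3 calls the assumed effect small, and that is for the EMA simulation. The sample size of 650 does not enter this point, and the article gives no figure of its own to reproduce here.

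**Assumptions.** SD 1 at each wave; true week-5 effect -0.20 SD; rho 0.6, range 0.5 to 0.7; the chance of staying is logistic in the observed baseline score.

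**Closed form.** Within an arm, expected change given baseline x is the arm effect minus (1 - rho) times (x - mean). Averaged over those retained:

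change contrast = effect - (1 - rho) x gap,

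where gap is the retained active baseline mean minus the retained waitlist baseline mean, in SD. So bias = -(1 - rho) x gap. At rho 0.6 a gap of 0.05 gives 0.4 x 0.05 = 0.02 SD, or 10% of 0.2.

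**Two-wave simulation, rho 0.6.** Slopes are log-odds of staying per SD of severity (-0.3 is an odds ratio of 0.74). Ranges span repeated runs.

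| Slope, active / waitlist | Retention, active / waitlist | Change contrast, retained set | Baseline-adjusted, retained set | All baselines kept |
|---|---|---|---|---|
| -0.3 / 0 | 50% / 50% | -0.141 to -0.144 | about -0.20 | about -0.20 |
| 0 / -0.3 | 50% / 50% | -0.259 to -0.261 | about -0.20 | about -0.20 |
| -0.3 / -0.3 | 40% / 60% | -0.177 to -0.181 | about -0.20 | about -0.20 |
| equal | equal | -0.196 | about -0.20 | -0.196 |

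In the first row the gap is about -0.146, so the formula gives bias = 0.4 x 0.146 = 0.058 and a contrast of -0.20 + 0.058 = -0.142, which agrees. With rho 0.5 / 0.6 / 0.7 the first row gives -0.127 / -0.144 / -0.156, the second -0.273 / -0.261 / -0.245 and the third -0.170 / -0.177 / -0.184.

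**Three-wave check of the actual rule** (week 5 or month 6 suffices; true effect zero; correlation 0.5 or 0.7; stronger assumed patterns, with log-odds of dropout per SD of 0 against 0.7, 0 against 1.0, or -0.5 against 0.5). The plan's set shows a spurious effect of 0.05 to 0.14 SD with about 30% lacking any follow-up, 0.09 to 0.24 SD at 50% and 0.13 to 0.31 SD at 70%. Keeping all baselines gives about 0, within about 0.03 SD of simulation error. With no dependence on severity, or the same dependence in both arms, neither set is materially biased.

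**Dropout driven by the unobserved week-5 score.** Here the ranking reverses. Two waves, rho 0.6, slopes -0.3 / 0: -0.259 for the retained-set change contrast against -0.294 with all baselines. In the three-wave check, week-5 bias is 0.06 to 0.30 SD in the plan's set and 0.10 to 0.48 SD with all baselines. At month 6 it is about 0 in the plan's set and 0.05 to 0.16 SD with all baselines.

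**The case against.** The strongest objection is that the exclusion does not by itself cause the bias. In the simulated scenarios, a baseline-adjusted model fitted only to the retained participants returns about -0.20. The article does not say whether baseline means are free, constrained or adjusted for, and a condensed article may leave that to the analysis plan. This stands. A reader might infer that the inclusion rule alone invalidates the secondary analyses; the text does not support that, because the bias needs the rule together with free baseline means.

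A second objection is that keeping every baseline helps only when dropout is explained by observed scores. If people leave because of how they are doing at week 5, the all-baseline model is the more biased there. This also stands, and such dropout is plausible in this population. Nobody should read the remedy as a general cure for dropout.

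Third, every magnitude is assumed. The Discussion warns of high dropout overall, not of dropout that differs by arm. That is right. The different access to materials makes a difference between arms plausible but does not show one.

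Fourth, the set is wider than completers: one of two follow-ups is enough. To say that only those who stayed to the end are compared would overstate the rule.

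None of this removes the point. The rule is stated outright, it discards usable data on randomised participants, and the article describes no model feature or further analysis that would offset it.

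**Conclusion.** The point holds in conditional form and should be acted on. It concerns the secondary outcomes only.

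The bias arises if (a) baseline is modelled with separate means per arm, as the wording suggests, and (b) dropout depends on baseline severity differently by arm, or equally but at different rates. Its size is then about (1 - rho) times the retained-arm baseline gap. With rho 0.6 and the milder assumed patterns it is about 0.02 to 0.06 SD, or 10% to 30% of an assumed 0.2 SD effect, and it can shrink or inflate the result. Stronger assumed patterns reach 0.31 SD. It is zero when dropout is the same in both arms.

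The effect size, correlation, retention and dropout slopes are all assumptions, because the article gives none of them. A claim that the secondary results will be biased, or in which direction, goes beyond the document.

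**What to change.** Replace the inclusion sentence for secondary outcomes in section 2.9 with text along these lines: the mixed-effects models include all randomised participants with a baseline questionnaire, analysed in the allocated group whether or not a follow-up was completed, with baseline means constrained equal across randomised groups (or baseline as a covariate).

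In addition:
- State that the minimal-exposure rule on module use does not apply to this analysis. It binds the intervention groups only and would otherwise reintroduce unequal selection.
- Keep the baseline-plus-one-follow-up set as a supportive analysis.
- Report retention by arm, and baseline severity by arm for those with and without follow-up.
- Add a sensitivity analysis for dropout that depends on unobserved follow-up scores.
- Confirm that the baseline battery is completed before allocation. Table 2 dates it only to week 1, and the equal-means constraint relies on this.

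The cost is a few sentences and one further analysis. No new data are needed, since the baseline questionnaires are collected anyway. The downside is that the main analysis then relies on dropout being explained by observed scores. If it is not, that analysis can be more biased at week 5 than the change contrast it replaces, which is why the sensitivity analysis belongs with it.

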### 2.10 Data management

As described above, all data will be collected continuously throughout the duration of the study *via* the *Nałogometr* mobile app, available on App Store and Google Play, and stored on a secured server. Key project personnel, i.e., Principal Investigators (PIs) and Co-Investigators (CIs) will be the data steward and will be responsible for documenting and managing the data during the collection, analysis, and publication phases. Additional project personnel, i.e., project coordinators, data analysts, and data scientists, will receive the data as per instructions from the PIs and CIs in an anonymized format. Following publication processes, the data will be archived and stored on a similarly secured server.

Data documentation will include codebooks that document the following: data collection protocols, methodology, and sample; description of specific data sources, e.g., types of measures that correspond to each raw data unit.

As per the needs of the particular project phase and according to current research questions, data will be queried and exported as ASCII files and made available to the additional project staff. Such datasets will include an individual (anonymized) participant identifier code, demographic information, relevant variable labels, and values. According to the current research questions, additional project staff will perform any data transformations necessary for the final and published analyses. Any publications that result from the data collected will be prepared only with the use of anonymized (de-identified) datasets and will pertain only to aggregate-level results. Due to the expected absence of (high) risks for participants of this study, establishing a data monitoring committee is not necessary.

It will be the responsibility of each additional staff member to produce documentation of what and how were the data used for the research task they were involved in. This will include documentation on the decisions related to any data transformations and coding performed (including variable lists and definitions of the raw data used and how the derived variables were produced), as well as the analytical methods and techniques performed for any particular research task.

## 3 Discussion

This study protocol describes a randomized controlled trial designed to determine the effectiveness of self-guided psychological intervention modules delivered *via* a smartphone app (*Nałogometr*). We aim to examine whether and which interventions can effectively reduce craving and lapse risk in problematic alcohol or stimulant use. The embedded trial and analysis will evaluate the effectiveness of intervention modules for alcohol or/and stimulants use. In exploratory analyses, we investigate whether user engagement moderates or changes in psychological functioning measures (e.g., sensation seeking, impulsivity, stress coping, emotion regulation) mediate the effectiveness of the interventions. We hope to determine if these interventions delivered through mobile devices can be effective and contribute to future prevention or therapy addiction programs. The wide availability and accessibility of developed interventions are a substantial advantage. Mobile app interventions may reduce treatment barriers by staying anonymous and avoiding stigma and may be especially useful in places where professional help is unavailable (49–52). We plan a 6 months follow-up to conduct a longer-term evaluation and check the sustainability of the potential change in the user’s behavior–it is an essential factor for relapse prevention through the management of craving. Such a complex study of 13 conditions will allow us to understand better which long-term interventions are most effective. We include multiple intervention types to better assess their effectiveness across diverse individuals. One limitation of the present study could be that the participant dropout will be higher than expected based on previous research (53, 54). Due to the lack of personal contact with researchers and no additional incentives, e.g., prizes or monetary remuneration, the commitment to participate throughout the study may be lower, and motivation may decrease over time.

## Ethics statement

The studies involving human participants were reviewed and approved by the Institute of Psychology Polish Academy of Sciences Ethics Committee. Written informed consent for participation was not required for this study in accordance with the national legislation and the institutional requirements.
